# To assess whether addition of pyriproxyfen to long-lasting insecticidal mosquito nets increases their durability compared to standard long-lasting insecticidal mosquito nets: study protocol for a randomised controlled trial

**DOI:** 10.1186/s13063-015-0700-7

**Published:** 2015-04-28

**Keywords:** Net durability, Insecticide resistance management, Malaria control, Insecticide-treated bed net, Pyrethroid, Pyriproxyfen, Insect juvenile hormone mimic, Clinical malaria, Entomological inoculation rate, Randomised controlled trial

## Abstract

**Background:**

The effectiveness of pyrethroid-treated bednets for malaria control in sub-Saharan Africa is under threat because of high levels of resistance to pyrethroid insecticides in the vectors. Here we assess the durability of polyethylene nets with a novel combination of permethrin, a pyrethroid, with pyriproxyfen, an insect juvenile mimic (PPF-LLIN), in comparison with a typical permethrin-treated long-lasting insecticidal net (LLIN).

**Methods:**

This is a cluster randomised controlled trial of net durability in Burkina Faso, with clustering at the level of the compound and includes entomological outcome measurements. Half the compounds in each village will be randomly allocated PPF-LLIN and half the LLIN. All sleeping places in a compound will be provided with one type of net. We will distribute the nets at the start of the first transmission season and follow net use at the start and end of each transmission season for 3 years. In one village, bio-efficacy and chemical content will be recorded immediately after net distribution and then at 6, 12, 18, 24, 30 and 36 months. In the other village net survivorship and fabric integrity will be recorded immediately after distribution, and then at 6, 12, 18, 24, 30 and 36 months. Routine measurements of indoor temperature and relative humidity will be made in both villages during the study. Residents will be followed for possible side effects of the PPF-LLIN by surveillance of known asthmatic subjects during the first month post-distribution and pregnancy outcomes will be monitored from antenatal clinic records.

**Discussion:**

The protocol is novel on two accounts. Firstly, it is the first to describe the procedure for measuring net durability following recent World Health Organisation (WHO) guidelines. Meeting the minimum requirements set in the guidelines is essential before a new type of net can be recommended by WHO’s Pesticide Evaluation Scheme (WHOPES). Secondly, it describes methods to monitor the persistence of an active ingredient that reduces vector fertility and fecundity. If the PPF-LLIN is both effective and persistent it will provide an alternative vector control strategy where pyrethroid-resistant vectors are present.

**Trial registration:**

ISRCTN30634670 assigned 13 August 2014.

**Electronic supplementary material:**

The online version of this article (doi:10.1186/s13063-015-0700-7) contains supplementary material, which is available to authorized users.

## Background

The massive scale-up of long-lasting insecticidal nets (LLINs) has contributed to a decline in malaria in many parts of sub-Saharan Africa (SSA) over the past decade [1,2]. Pyrethroids remain, until now, the only class of insecticide used for treating nets since they are highly insecticidal and safe to use [3]. However, the rapid increase in resistance to pyrethroid insecticides in mosquitoes may jeopardise future malaria vector control [4]. Polyethylene nets, containing a novel combination of permethrin, a pyrethroid, and pyriproxyfen (PPF-LLIN), an insect juvenile hormone mimic [5-8], may enhance malaria control, as well as reducing the spread of pyrethroid-resistant mosquitoes.

A two-armed cluster-randomised controlled trial (AvecNet) [9] is being conducted near Banfora, Burkina Faso, to assess whether PPF-LLINs (Olyset Duo nets containing 2% permethrin, 1% pyriproxyfen w/w) provide better protection against clinical malaria in children than 2% permethrin-treated LLINs (Olyset Nets) in an area with high levels of pyrethroid resistance in the main vector, *Anopheles gambiae s.s*. [10]. At the start of the study, 33% mortality was obtained after exposure to a discriminating dose of permethrin (0.75% papers for 1 hour exposure) and the time to kill 50% after exposure to the discriminating dose was 91 minutes. In the current study we propose to measure the durability of both PPF-LLINs (Olyset Duo) and LLINs (Olyset), used as a control, under operational conditions for 3 years to complement the efficacy results of the main trial. Since all villages in the main trial will have PPF-LLINs by the end of the 2-year trial, this durability study will take place in villages outside the main trial and adverse events (AE) will be monitored as for the main trial.

Recently it has become apparent that while the Olyset brand of LLINs has excellent tensile strength and insecticidal properties that last for many years, the netting is prone to develop elongated holes due to the weave unravelling once a small hole develops. Thus, large-scale surveys, supported by the President’s Malaria Initiative, of national LLIN distributions in several African countries found that after 2 years of domestic use, Olyset nets sometimes scored badly on fabric integrity in comparison to many other brands [11]. The manufacturer has acted on these findings and changed the knitting pattern of the Olyset Net, which inhibits the development of elongated holes, so that since late 2013 all Olyset Nets manufactured have this new knitting pattern ([name], personal communication). In our durability trial we will use new knitting pattern nets for both the PPF-LLIN and LLIN. Durability of PPF-LLINs and LLINs will be assessed using 3 criteria: (1) net survivorship, (2) fabric integrity and (3) insecticidal activity (bio-efficacy). This protocol follows the recommendations made by WHO in 2013 entitled ‘*Guidelines for monitoring the durability of long-lasting insecticidal mosquito nets under operational conditions*’ [12], WHO’s 2013 ‘*Guidelines for laboratory and field testing of long lasting insecticidal nets*’ [13] and WHO’s Vector Control Technical Expert Group’s guidelines on ‘*Estimating functional survival of long-lasting insecticidal nets from field data*’ [14].

This protocol is the first we know of that adheres to these guidelines. It therefore serves as an exemplar for other studies wishing to adopt these criteria.

### Study objectives

#### Primary objective

To determine whether the bio-efficacy of PPF-LLINs is superior to that of LLINs for the first 36 months after net distribution.

#### Secondary objective

To determine the physical integrity of LLIN and PPF-LLINs for the first 36 months after net distribution.

#### Tertiary objectives

To determine the survivorship of LLIN and PPF-LLINs for the first 36 months after net distribution.To measure the content of permethrin in LLINs and permethrin and PPF in PPF-LLIN netting for the first 36 months after net distribution.To document AE that may be associated with PPF-LLIN use.

## Methods/Design

### Study area

The study will be carried out in two villages in the Cascades Region of Burkina Faso. In Dalamba (village A) samples will be cut from nets and the nets will be replaced (Primary objective and Tertiary Objective 2) and Sanako (village B), where nets will be left intact (Secondary objective and Tertiary Objectives 1 and 3). AE will be followed in both villages. The separation of activities in two villages is designed for operational reasons to simplify data collection and analysis since in village A nets will be replaced through the course of the trial, whilst in village B nets will be delivered and hung only at the start of the trial. This arrangement is also less likely to create dissatisfaction amongst those who will not get replacement nets. The study villages have a total population of approximately 2,000 and are situated close to the south-east of Banfora (10° 56′ 00″ N, 004° 46′ 00″ W) in an area of open Sudanian savannah. These villages are located near those enrolled in the main AvecNet Trial, but are outside the main study area. Most people in the main trial and in this study live in houses made with mud or cement walls and thatched or metal roofs. The climate is tropical with most rain falling from May to October. This defines the highly seasonal malaria transmission with most malarial episodes experienced during or immediately following the major rains. The study’s field station is based at Banfora town, which is the main town in the district. This is an area of cotton-growing since 1968 with *An. gambiae* S forms predominating over M forms [15].

### Net owner enrolment

As is customary in Burkina Faso, sensitisation will start by discussions with community elders and then representatives of the villages in order to explain the nature of the study and what will be required during the study (information sheet, Additional file 1). The key attendees names and roles will be documented for each village.

We will explain to individual net owners the purpose of the study and will provide them with an information sheet (Additional file 1). Witnessed written consent (Additional file 1) will be obtained from each participant, before net donation and exchange of their previous net. We will also seek written consent from net owners before taking netting samples. During these procedures it will be made clear that subjects and households will be able to leave the study at any time without giving a reason but their original net will not be returned. Given the nature of the study we will also encourage participants to keep the nets they are given and not to exchange them. We envisage that most study subjects will be enrolled at the start of the study for 36 months. Occasionally, due to movement of residents into the villages, some subjects join during the study.

### Randomisation and blinding

Both types of net will be randomly allocated to compounds, with allocation stratified by compound size in both villages. In village A 6 different compounds will be sampled in each study arm at 7 sequential time points: thus, 84 compounds (42 for each study arm) will be selected randomly, without replacement, at the start of the study. The remaining compounds in the village will be randomly assigned equally to the intervention or control and will act as reserve compounds in case of withdrawal of those randomised. At each sampling time point 4 nets will be randomly selected from each of the pre-selected compounds: that is within 1 to 2 weeks of hanging and then 6, 12, 18, 24, 30 and 36 months later. As holes will be cut in the selected nets to provide netting samples for laboratory testing, the nets will be taken from the recipient and replaced with a new one of the same type: that is LLINs will be replaced with LLINs and PPF-LLINs replaced with PPF-LLINs. A total of 649 nets will be distributed in Dalamba (village A) and 541 in Sanako (village B). In cluster-randomised controlled trials it is particularly important to minimise imbalance for factors likely to be correlated with the outcome; bio-efficacy will probably be affected by net washing and possibly by the ambient temperature and humidity, this will be corrected for in the analysis. Observer bias will be reduced where feasible. Both types of nets will be of a similar shape and colour and will be blinded before distribution, see below. Thus, end-users, field workers conducting the physical integrity/survivorship surveys and technicians conducting the bio-efficacy, fabric integrity and insecticide content tests will be blinded to the type of net. A standard questionnaire will be used to collect data from the net user at each follow-up. The processes of the interventions, both for PPF-LLINS and LLINs, will be closely monitored not only for quality but also to document any bias between the clusters and villages.

### Interventions

The LLINs and PPF-LLINs distributed will be manufactured by Sumitomo Chemical Company (Japan) and are the same as those being used in the main AvecNet Trial, model ‘Extra Family’ rectangular (180 cm wide × 190 cm long × 150 cm high), except that these will have been manufactured using the improved (new) knitting pattern. The LLINs are WHO recommended and meet WHO specifications (http://www.who.int/whopes/Long_lasting_insecticidal_nets_Aug09.pdf) with 2% w/w permethrin incorporated into polyethylene fibres. The PPF-LLINs contain 2% w/w permethrin and 1% w/w pyriproxyfen incorporated into polyethylene fibres. Olyset Duo was submitted to WHOPES in August 2012 and has recently completed Phase I testing. These nets will be distributed at the beginning of the main transmission season, at no cost to the recipients. Government Roll Back Malaria information, education and communication procedures will be followed to encourage correct net use and maintenance. The storage and distribution of the LLIN and PPF-LLIN will follow the same procedures as detailed in the main AvecNet Trial Protocol (submitted June 2014). In addition, as this trial will be blinded for the recipients and survey field assistants and laboratory staff, nets will be given sequential unique identity (ID) numbers in the top right hand corner of the label and all mention of ‘Olyset’ and ‘Olyset Duo’ removed before the start of net distribution. This will include blinding or replacing bags in which the nets are supplied from the manufacturers. The ID and net type will be noted on specific forms, which will kept in a sealed envelope and locked under the supervision of the Principal Investigator (PI) until the datasets are finalised and locked.

The date the nets are given to the householder will be written under the unique identifier at the time of donation so that all nets will be numbered with a unique ID number and the date of issue. The recipient’s name, net number, date of donation and identity of the compound and household to which they were distributed will be recorded on the clinical report form (CRF) at the time of delivery. The household identification, name of head of household, and global positioning system (GPS) coordinates will be recorded at the baseline demographic survey. Both types of net will be the same design and colour so that study participants will be blinded to the net allocation. However, each net ID will be coded and the location and recipient recorded as indicated above and this information will be collected at each survey to keep track of the identity of each net.

### Study procedures and evaluations

The study villages will be enumerated following normal demographic surveillance procedures and compounds mapped before being randomised to net type. It is intended that LLIN distribution will be completed by July/August 2014. Nets selected for monitoring will be identified by their unique ID, date of donation and located by the village, household number, name of the head of household and user name. Net users who have moved, and taken their nets with them, or withdrawn consent will be recorded on the survey form and on the master list and they will be replaced by another net user from the same compound. If an entire compound refuses to participate another compound will be randomly selected from those remaining.

Surveys will be conducted in village B at 0, 6, 12, 18, 24, 30 and 36 months post-distribution for all endpoints. A standard questionnaire will be used to collect data at each follow-up from the net user, or parent/carer in the case of children. The following information will be recorded: whether the net is hung over the sleeping place at the time of visit, whether it is in storage, being washed, given away or discarded, the method of hanging, whether it can be tucked securely under the mattress all around, and the fabric integrity and the condition of the net. In village B all available nets will be surveyed each time point, in village A only the compounds randomised for sampling at each time point will be surveyed.

### Net selection and sampling

Village A will be used to sample nets for bio-efficacy assay and the measurement of insecticide content, as detailed in ‘randomisation and blinding’ above. Samples will be cut from the nets while they are hanging in the villages. The bio-efficacy assay requires 3 samples of 25 cm^2^ from each net (Positions 2, 3 and 4; see Figure 1). Following the WHO guidelines [10,11] the measurement of insecticide content will made on 5 pieces of 30 cm^2^ from each net immediately after distribution (positions 1 to 5 in Figure 1) and 4 pieces of 30 cm^2^ from each net 6, 12, 18, 24, 30 and 36 months later (positions 2, 3, 4 and 5). The bio-efficacy samples will be wrapped individually in aluminium foil but all the samples taken to measure insecticide content from a single net will be wrapped together. After wrapping in foil the samples will be labelled with the type of assay, the date of sampling and the net ID plus the position sampled (for example, 092–3 is net ID 92, cut from position 3). Samples will be stored at +4°C, and left for 24 hours at room temperature until assayed.

**Figure 1 Fig1:**
[figure not shown]
Position of samples taken from each panel of the bednets [12].

Village B will be used to measure net survivorship and fabric integrity immediately after net distribution and then 6, 12, 18, 24, 30 and 36 months later.

### Bio-efficacy (Dalamba, village A)

Bio-efficacy tests will use the net samples from village A and will be conducted in laboratories. The knockdown, mortality and blood feeding tests will be conducted in Burkina Faso while those for egg production and production of viable larvae will be conducted at the Liverpool School of Tropical Medicine, UK.

### Mosquitoes

The knockdown and mortality tests will use a standard laboratory colony of permethrin-susceptible *An. gambiae* s.s. (Kisumu strain) aged 2 to 5 days old without blood feeding. The tests for egg and larvae production will use standardised laboratory colonies of permethrin-resistant *An. gambiae* s.s. (Tiassale strain) with blood feeding. This resistant colony will be submitted to regular quality testing, both phenotypic and genotypic, during the study to control for any changes in resistance levels.

### Test procedures

Measuring knockdown and mortality

Knockdown and mortality will be measured using WHO cone bioassays [12]. Since 3 net samples will be cut from each net, there will be 72 netting samples to be tested for each arm at each time point and a total of 1,008 samples overall. Two standard WHO cones are fixed with a plastic manifold onto each of the three netting pieces, one at a time. Five permethrin-susceptible, non-blood-fed, 3- to 5-day-old female *An. gambiae s.s.* will be exposed for 3 minutes in each cone and then held for 24 hours with access to 6% sugar solution. Knockdown will be measured 60 minutes after exposure, and mortality measured after 24 hours. A negative control, from an untreated net, will be included in each round of cone bioassay testing. Bioassays will be carried out at 27 ± 2°C and 80 ± 10% relative humidity. Bioassay results for the netting pieces from each sampled net will be pooled to determine if the net meets the WHO efficacy requirement: that is ≥ 80% mortality. If the net fails these criteria, a tunnel test will be conducted on one of the four net samples that caused mortality closest to the average mortality in the cone bioassay [12].b)Measuring egg production and viable offspring

Here the assay is designed to mimic what is likely to happen in nature by measuring egg and larval production in blood-fed, permethrin-resistant mosquitoes after exposure to the netting samples. Batches of 10, 3-day-old unfed mosquitoes will be exposed to LLIN, PPF-LLIN or untreated netting samples for 3 minutes using WHO cone bioassays [10]. At each net sampling time point, the same three panels will be tested for the six nets sampled from the field for each of the two types of netting. In addition a control untreated netting will be tested in duplicate. So for each of the 7 time points, 380 mosquitoes are tested (10 mosquitoes/test × 3 net panels/net × 6 nets/net type × 2 net types, plus 2 control nettings).

After exposure to the netting samples the female mosquitoes will be transferred to cages containing an equal number of newly emerged male mosquitoes and provided with 6% glucose solution *ad libitum*. Then, 24 hours after exposure to the netting samples the female mosquitoes will be fed on animal blood using membrane feeders for 25 minutes and any unfed mosquitoes recorded and discarded. After feeding, gravid mosquitoes will be individually placed into 15-cm^3^ cages, provided with an oviposition substrate of tap water in a 100 ml glass cup and left overnight to lay eggs. The following morning the number of eggs laid by individual females will be recorded. Eggs laid by each female will be transferred into individually-labelled plastic cup and the number of eggs hatching every 24 hours will be monitored for 3 days.

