### Sample size rationale

#### Primary outcome

##### Bio-efficacy - measured in Dalamba, village A

WHO expects that LLIN netting will kill at least 80% of mosquitoes that land on it. In this trial, however, the effects of the PPF-LLIN netting are not just on killing mosquitoes, but also causing sterility and reducing the number of offspring produced by female mosquitoes. A 50% reduction in killing when exposed to LLINs nets is likely to impact malaria vector control, as is a 50% decrease in the proportion of gravid females laying eggs after exposure to PPF-LLINs. In order to detect 50% reduction in killing from 80% to 40% and a coefficient of variation between clusters of 0.25, a conservative estimation, one requires 6 compounds with 4 nets, each with 3 netting samples/net/time, in each cluster to demonstrate a statistically significant impact at the 5% level and with 80% power. These calculations are based on the formula of Hayes and Bennett for clustered data [18]. For the 7 time points, one needs to recruit forty two compounds to each study arm.

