## Discussion

Insecticide-treated bednets are a highly effective vector control tool [19] but their future success is threatened by the spread of vectors resistant to pyrethroids [4], which is presently the only class of insecticide used for treating bednets. Finding alternative strategies to deal with the problem of insecticide resistance is a priority for malaria control and strategies leading to elimination [20]. Since bednets are effective methods of malaria control and have been used in their millions across SSA, insecticide resistance strategies that focus on bednets have much to recommend them. Here, we test a new net with a combination of two active ingredients: permethrin, a pyrethroid, and pyriproxyfen, a juvenile hormone mimic. Unlike permethrin, the principal mode of action of pyriproxyfen is not to kill mosquitoes, but to reduce their fecundity and fertility following a blood meal [6-8].

Ideally, the new combination must be effective for several years in order for it to be a useful public health intervention and to be recommended by WHOPES. In this trial we follow the recent recommendations made by WHOPES for assessing the durability of LLINs [12] and describe them in a protocol for others to adapt. Net durability will be assessed using a number of criteria. Specifically, this includes measuring the bio-efficacy and chemical content in the nets over time in one village, as well as the net survivorship and fabric integrity in a separate nearby village. Although we think it unlikely that there will be any adverse reactions to the new net containing pyriproxyfen we will record any AE in asthmatics and pregnant women.

The chemical measurement with time will give an indication of the longevity of the pyrethroid and pyriproxyfen in polyethylene netting in a typical rural village setting and the bioefficacy measures will give an indication of the activity of these compounds on the surface of the netting. The study is being run for 3 years as this is the current estimation of time between large-scale donation campaigns adopted by WHO and donor agencies, which balances expected net survival time and cost.

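### The primary sample size and its 80% power cover killing only; viable offspring is assayed on a quarter of that netting and has no power figure of its own

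*Protocol article*

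**What the plan says.** The Primary objective is one of superiority: "To determine whether the bio-efficacy of PPF-LLINs is superior to that of LLINs for the first 36 months" after distribution. Study endpoints gives primary bio-efficacy two components, 24-hour mortality and viable offspring relative to control.

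The Sample size rationale for the primary outcome works through killing: "In order to detect 50% reduction in killing from 80% to 40% and a coefficient of variation between clusters of 0.25". It concludes that "one requires 6 compounds with 4 nets, each with 3 netting samples/net/time, in each cluster to demonstrate" significance at the 5% level with 80% power. It also calls a 50% fall in egg-laying important, but gives that outcome no baseline rate, variance or calculation.

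Randomisation and blinding agrees with this for sampling: 4 nets from each of 6 compounds per arm at each of 7 time points. Test procedures agrees for mortality: 72 samples per arm per time point and 1,008 overall.

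For eggs and larvae, Test procedures says something else: "the same three panels will be tested for the six nets sampled from the field for each of the two types of netting". Its count of 380 mosquitoes per time point confirms six nets per type. The text does not say how these six relate to the 24 nets sampled or to the 6 compounds.

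Three further statements bear on which component carries the superiority question. Both nets contain 2% permethrin (Interventions). On strains, "The knockdown and mortality tests will use a standard laboratory colony of permethrin-susceptible" *An. gambiae* (Mosquitoes). And "the principal mode of action of pyriproxyfen is not to kill mosquitoes" but to reduce fecundity and fertility (Discussion).

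**The concern.** A reader of the Sample size rationale will take the 6 × 4 × 3 design and its 80% power as the justification for the primary outcome as a whole. It justifies one component. The other is run on a quarter of the netting, for a reason the text does not give.

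The gap falls in an awkward place. With the same permethrin content in both nets and a susceptible strain in the mortality test, the document gives little reason to expect a 40-point difference between arms in killing. The benefit of adding pyriproxyfen should mainly appear in offspring. So the contrast with a power figure is not the one on which a superiority effect is mainly expected. If single time points are interpreted, a non-significant offspring result at, say, 36 months could reflect either loss of pyriproxyfen activity or too little netting, and the plan gives no basis for telling these apart.

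**Working it through.** **Counts**
- Mortality: 6 × 4 × 3 = 72 samples per arm per time point; 72 × 2 × 7 = 1,008. Both match the text.
- Offspring: 10 × 3 × 6 × 2 = 360, plus 2 × 10 control mosquitoes = 380. This also matches. Netting per arm is 6 × 3 = 18 samples, and 18/72 = one quarter.

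**Inputs from the Sample size rationale:** p0 = 0.80, p1 = 0.40, k = 0.25, 5% level (two-sided assumed, as sidedness is not stated), 80% power, Hayes and Bennett formula.

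**Formula**

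c = 1 + (1.96 + 0.84)² × V / (p0 − p1)², where V = [p0(1 − p0) + p1(1 − p1)]/n + k²(p0² + p1²) and (1.96 + 0.84)² ≈ 7.85.

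For 80% v 40%: V = 0.40/n + 0.0625 × 0.80 = 0.40/n + 0.05, and (p0 − p1)² = 0.16.

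**Reproducing the plan's 6 compounds**
- n = 12 netting samples: V = 0.0833, c = 1 + 7.85 × 0.0833/0.16 = 5.09, rounded up to 6.
- n = 4 nets: c = 8.36, so 9.
- n = 120 mosquitoes: c = 3.62, so 4.

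Of the variants tried, including one-sided ones, only the netting sample as unit with a two-sided test gives 6.

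**Offspring assay with 6 compounds per arm, one net per compound assumed, killing inputs borrowed**

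Power = Φ(√[(c − 1)(p0 − p1)²/V] − 1.96), with c = 6, so (c − 1)(p0 − p1)² = 0.80.

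| Unit and n per compound | V | Power with 6 | Compounds for 80% |
|---|---|---|---|
| Killing as planned, 12 samples | 0.0833 | 87% | 6 |
| Offspring, 3 samples | 0.1833 | 55% | 10 |
| Offspring, effective n = 10 mosquitoes | 0.0900 | 85% | – |
| Offspring, 15 mosquitoes | 0.0767 | 90% | 5 |
| Offspring, 30 independent mosquitoes | 0.0633 | 94% | 5 |

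Between these ends, the design effect 1 + 29ρ for 30 mosquitoes on one net, with an assumed within-net correlation ρ of 0.1, 0.2 or 0.3, gives 80%, 67% or 56%.

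**Sensitivity, per time point, 50% relative reduction**
- n = 3: 45% at a 70% baseline, 28% at a 50% baseline.
- n = 30: 90% at 60%, 86% at 50%, 79.5% at 40%.
- n = 30, 80% baseline: 86% at k = 0.30, 76% at k = 0.35, 66% at k = 0.40.

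**Pooled over the 7 time points (c = 42 per arm, least favourable n = 3)**
- 80% v 40%: √(41 × 0.16/0.1833) − 1.96 = 4.02, power above 99%.
- 50% v 25%: V = 0.4375/3 + 0.0625 × 0.3125 = 0.1654; √(41 × 0.0625/0.1654) − 1.96 = 1.98, power about 98%.

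This assumes a similar effect at every time point and k = 0.25 throughout.

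**Same panels, more nets**

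Let f be the share of within-compound variance that lies between nets. Three panels of one net give the compound mean a within-compound variance proportional to f + (1 − f)/3. One panel from each of three nets gives 1/3. The ratio is 1 + 2f, so an assumed f of 0.2 to 0.6 means a reduction by a factor of 1.4 to 2.2.

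**The case against.** The strongest reply is that no stated figure is wrong. The 80% power is attached to killing, where it reproduces, and every count in the document adds up. A reader might infer that the 80% claim has been disproved for offspring. It has not, because the protocol makes no such claim there. What stands is that the power for offspring is unsupported.

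A reader might also infer that power for offspring is 55%. That needs three things the document does not supply: one net per compound, the killing rates and k carried over, and each netting sample counted as one yes/no result. The assay in fact records eggs and hatching for each female, and counting mosquitoes gives far higher power. This is a fair correction, and only a range can be defended. The upper end is not secure either. It needs 30 independent females on one net, while unfed females are discarded, and with one net per compound k has to absorb net-to-net variation as well. The text calls the assumed value, "a coefficient of variation between clusters of 0.25, a conservative estimation", but offers no data for either endpoint.

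The planned analysis models activity over time adjusting for compound, and the objective spans 36 months. On that reading the superiority question is well powered for a 50% reduction. This stands and limits the consequence to time-specific conclusions. It also rules out adding up error rates as if two endpoints at seven time points were fourteen independent tests; the plan does not describe such tests.

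Finally, a reader might infer that offspring is the only endpoint on which the arms can differ. That goes too far. The two nets may retain permethrin differently, and the Discussion says survival of resistant mosquitoes is measured too. The 80% to 40% contrast can also be read as decline from the WHO benchmark rather than as an expected gap between arms.

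**Conclusion.** The concern holds in a limited form. The stated sample size and 80% power apply to killing and do not carry over to viable offspring, which is assayed on 6 nets (18 samples) per arm per time point instead of 24 (72) and has no calculation of its own.

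Per-time-point power for offspring is undetermined, at about 55% to 94% on the plan's borrowed inputs with one net per compound, and below that range with a lower baseline or a larger k. Pooled over 42 compounds per arm it is about 98% or more for a 50% reduction at baselines of 50% to 80%, even on the least favourable of the units in that range. The main superiority question is therefore probably safe if it is answered by the pooled contrast; statements about single time points are not. All these figures assume a two-sided 5% test and inputs that the document states for killing only.

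**What to change.** 1. In the Sample size rationale, say that the 80% power applies to killing.
2. Reconcile the six nets in the offspring assay with the 24 sampled, and state how the six map to compounds.
3. Give power for viable offspring as assayed, as a range, with its own baseline rate, between-net variation and unit of analysis.
4. State that the superiority conclusion for offspring rests on the arm contrast over all time points (42 compounds per arm), in line with the planned modelling over time, and that results at single time points are descriptive or of limited power.
5. Keep the 380 mosquitoes but test one panel from each of three of the four sampled nets per compound, rotating positions 2 to 4, in place of three panels of one net (if the six nets are one per compound). This lowers the within-compound variance of the compound mean whenever nets differ.

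Items 1 to 4 are changes of wording plus a short calculation. Item 5 changes only which already-cut samples are used and needs no extra nets or mosquitoes. Its cost is fewer panels per net, so each net's own result is less precise and differences between positions can no longer be studied within a net.
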